## BACKGROUND

For patients, healthcare professionals and policy makers to make informed choices about healthcare they must have information about the effects of interventions that is valid and understandable. The manner in which this information is presented affects how it is understood and subsequent decisions.1,2  The objective of the Health Information Project: Presentation Online (HIPPO) is to improve communication of information about the effects of healthcare based on randomized trials of alternative ways of presenting this evidence.

This is the first HIPPO trial. Information about the effects of drugs used to decrease cholesterol blood levels was chosen for this study because it is a common problem and high quality evidence is available on the effects of cholesterol-lowering drugs (statins).3 The results of this study will help to inform decisions about how best to communicate the benefits of statins to healthcare professionals (general practitioners), individual patients and the general public.

This study is also a pilot study intended to test the methods that we will use in future HIPPO studies. We have therefore selected comparisons for which there exists prior research evidence. Two systematic reviews have concluded that the use of the relative risk reduction (RRR) to express the relationship between two probabilities results in individuals having a larger estimate of that relationship and being more likely to decide to treat compared with the use of an absolute risk reduction (ARR) or number needed to treat (NNT).1,2 None of the studies included in these reviews has investigated the relationship between the summary statistic that is used and the extent to which decisions are congruent with “expected utilities”.

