Expected utility (or “expected value”) can be defined as follows: Under uncertainty where there is a p% chance of an outcome (X), say having angina or a heart attack, the expected utility is equal to pּUx + (1-p)ּUnot x where Ux represents the desirability (utility value) of the outcome and Unot x is the desirability of the alternative outcome (good health). If there is a p% chance of X and a q% chance of another outcome (Y), then the expected value is equal to [pּUx + (1-p)ּUnot x + qּUy + (1-q)ּUnot y]. Expected utility theory suggests that people making rational decisions should choose the option with the highest expected utility.4 The utility of outcomes, such as different health states, is usually expressed as being between zero and one (e.g. with death having a value of zero and a fully healthy life having a value of one, although some people consider some health states to be worse than death).

Expected utility theory has been questioned for a number of reasons, including problems with how utilities are measured and observations that people often do not, in fact, choose to maximize their utilities.5-9 Nonetheless, it can still be argued that as the expected utility for a decision, such as to take statins, increases one would expect that, on average, increasing proportions of people would choose to take the pills, if they are well informed. This argument does not depend on every individual choosing to maximize her utilities. Some people may make decisions based on other factors and it is difficult to accurately measure people’s utilities. Nonetheless, one would expect some degree of correlation between the expected utility of deciding to do something, such as taking pills, and the proportion of people who decide take the pills. The assumption underlying this study is that ways of presenting information about the effects of healthcare that result in decisions that are most consistent with individuals’ subjective expected utilities are best.

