## METHODS

### Study design

The study is a Web-based randomized trial in which participants will be randomized to one of six ways of presenting information about CVD risk reduction listed above. The relative importance of the consequences of starting statins will be elicited in two ways (VAS’s and LTRS’s) for all of the participants. The order in which this is done will be randomized.

A printout of the Webpages that will be used is attached [Available as a supporting PowerPoint file, Figure S3.1 Facimile HIPPO Webpages for protocol]. Upon logging into the study Website, participants will be given information about the study and asked to give informed consent to participate. They will be presented with a brief scenario in which they are asked to imagine that they have elevated cholesterol and are given the option of taking pills that lower cholesterol (statins). The relative importance of CVD risk reduction, taking pills and costs will be elicited using VAS’s and LTRS’s. They will then be presented with information about the effect of statins on the risk of heart disease, using one of the presentations listed above, the need to take a pill each day and the out-of-pocket costs; and asked whether they would decide to take the pills or not. Baseline risk will then be altered in the direction that shifts the expected utilities towards the opposite decision; i.e. the baseline risk will be increased for respondents who decide not to take the pills and decreased for those who decide to take the pills. Participants will then be asked what they would decide again. After this they will be asked questions about their decision and about themselves and, finally, they will be asked which of the six ways of presenting CVD risk reduction they would prefer.

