### Analysis

We have the following variables:

UCVD = utility of having heart disease; i.e. 1 – how difficult it would be to have cardiovascular (“heart”) disease on a scale from 0 to 1; 1 equals the most difficult

UPill = utility of having to take a pill each day; i.e 1 – how difficult it would be to have to take a pill each day on a scale from 0 to 1; 1 equals the most difficult

UCost = utility of not having to pay for pills; i.e. 1 – how difficult it would be to have to pay an additional amount of money each month for equivalent to the out-of-pocket cost of taking a statin on a scale from 0 to 1; 1 equals the most difficult

PP = probability of having heart disease with taking pills

PN = probability of having heart disease without taking pills

Using these variables we can calculate the expected utility (EU) for a decision to take pills:

EU(taking pills) = PPּUCVD + (1 - PP)ּ(1-UCVD) – (1-UPill) – (1-UCost)

Operationally this transforms to:

EU(taking pills) = PPּ(1-VAS_hrt) + (1 - PP)ּ(VAS_hrt) – (VAS_pill) – (VAS_cost)

or not to take pills:

EU(not taking pills) = PNּUCVD + (1 - PN) ּ (1-UCVD)

Operationally this transforms to:

EU(not taking pills )= PNּ(1-VAS_hrt) + (1 - PN)ּ(VAS_hrt)

and the difference between these (A):
A = EU(taking pills) – EU(not taking pills)

The difference in expected utilities can range from positive values (in favour of taking pills) to negative values (in favour of not taking pills).

If G is used to represent the presentation group to which a participant is randomised and D represents the decision to take pills or not, then the relationship between D and A can be modelled as follows:

(Eq 1)          logit(D) = 0 + 1A

To examine the relationship between the model of what participants might be expected to decide based on the expected utilities of the two options (Eq 1) with how the information was presented, Eq 1 will be fit for each group G. We will then compare the fit between different groups by comparing the R2 between the different groups.

Using a maximum-likelihood model will allow us to adjust for other factors (age, gender, profession) in a natural way. This allows us to test for differences in professional background (scientists or engineers vs GPs or other health professionals vs others), and differences across countries (Canada vs Germany vs Norway vs USA). To the extent that any of these factors are confounders, adjusting for these factors would improve the precision of our model.

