### Sample size

Random variation in choices can be expected to be smaller the better risk information is understood. So we will expect a stronger association (larger R2) between the expected utility model (A) and what participants decide (D) the better the information about the risk of heart disease is understood. Turning this around, a significantly stronger association between the model and what participants decide for one presentation (G1) compared with another (G2) suggests that the first presentation was better understood than the second.

The detectability of a difference in magnitude between population R’s is not a simple function of the difference.10 That is, if we were to define j = R1 – R2 and try to use j as the effect size, the detectability of j under fixed conditions of  (level of significance) and sample size n, is not constant, but depends on where along the R scale the difference j occurs. The Fisher Z transformation of R provides a solution to this, and the effect size index q = Z1 – Z2 gives values whose detectability does not depend on whether the Z’s are both small or both large. Cohen considers q = 0.10 as a small effect size, and the following pairs of R’s illustrate this amount of difference: (0.00;0.10), (0.20; 0.29), (0.40; 0.48), (0.60; 0.66), (0.80,0.83), (0.90;0.92), (0.95;0.96). A medium effect size is q = 0.30 and the following pairs of R’s illustrate this amount of difference: (0.00;0.29), (0.20; 0.46), (0.40; 0.62), (0.60; 0.76), (0.80,0.89), (0.90;0.94), (0.95;0.97). A large effect size is when q = 0.50. This is illustrated by the following pairs of R’s: (0.00;0.46), (0.20; 0.61), (0.40; 0.73), (0.60; 0.83), (0.80,0.92), (0.90;0.96), (0.95;0.98).

As we have no prior information about the size of R within any of the information groups, we will conduct a pilot study. The number of subjects to be included in each group in the pilot study is based on power calculations for detecting a medium and a somewhat larger effect size (assuming equal size of the groups):

| q |  (2-sided test) | Power | N |
| --- | --- | --- | --- |
| 0.30 | 0.05 | 0.70 | 140 |
|  |  | 0.75 | 157 |
|  |  | 0.80 | 177 |
|  | 0.10 | 0.70 | 108 |
|  |  | 0.75 | 123 |
|  |  | 0.80 | 140 |
| 0.40 | 0.05 | 0.70 | 80 |
|  |  | 0.75 | 90 |
|  |  | 0.80 | 101 |
|  | 0.10 | 0.70 | 62 |
|  |  | 0.75 | 70 |
|  |  | 0.80 | 80 |

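### Comparing R2 between separately fitted arms mixes how closely decisions follow A with how many people choose pills, and ignores the sign of the slope

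*Protocol*

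**What the plan says.** Under Analysis in the protocol, Eq 1 is a logistic regression of the decision D on A, fitted once per presentation group. The comparison of presentations is then: "We will then compare the fit between different groups by comparing the R2 between the different groups". The type of R2 is not named.

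The Sample size section gives the interpretation: "So we will expect a stronger association (larger R2) between the expected utility model (A) and what participants decide (D") the better the risk information is understood. In reverse, "a significantly stronger association between the model and what participants decide for one presentation (G1) compared with another (G2") is taken to mean that the first presentation was better understood. The planning scale is q = Z1 - Z2, the difference between Fisher-transformed R's, with a table for two-sided alpha of 0.05 and 0.10.

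The Background reports from two systematic reviews that the relative risk reduction (RRR) leads to people "being more likely to decide to treat compared with the use of an absolute risk reduction (ARR") or the number needed to treat. It also gives the expected direction: "one would expect some degree of correlation between the expected utility of deciding to do something, such as taking pills", and the proportion who choose the pills. Neither Analysis, Sample size nor the alternative analyses in Attachment 1 requires the slope to be positive.

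**The concern.** The objective is congruence: how closely decisions follow people's own values. In Eq 1 that is the slope on A. The intercept carries the general readiness to take pills, and Eq 1 leaves it free in each arm. R2 depends on both. Two arms whose decisions follow A equally well can therefore differ in R2 only because more people in one of them say yes. That is the kind of difference the Background expects between presentations, so the artefact falls on the comparison of interest. It is a bias and not noise, so a larger trial makes a false difference more likely to reach significance.

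R2 also has no direction. An arm whose decisions ran against its utilities would score as well as an arm equally strongly in line with them.

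At stake is the trial's main conclusion, namely which presentation yields decisions most consistent with values.

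**Working it through.** **1. The plan's own table.** For two independent correlations, N per group = 2[(z(1-alpha/2) + z(power))/q]^2 + 3. With q = 0.30, alpha = 0.05 and power 0.80: 2[(1.960 + 0.842)/0.30]^2 + 3 = 177.4; the table has 177. All 12 entries reproduce to within one subject. So the table sizes one two-group comparison at full alpha, with variance 1/(n-3) per arm on the Fisher scale.

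**2. R2 with equal slopes.** The protocol gives no shares and no slope. Assumed here: A standard normal, slope 1 logit per SD in every arm, and only the intercept changed to give the stated share choosing pills.

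| Share | Fisher Z of r | Cox-Snell | Nagelkerke | McFadden |
|---|---|---|---|---|
| 50% | 0.439 | 0.170 | 0.227 | 0.135 |
| 70% | 0.407 | 0.149 | 0.211 | 0.132 |
| 80% | 0.361 | 0.120 | 0.190 | 0.128 |
| 90% | 0.279 | 0.074 | 0.156 | 0.119 |

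The pattern is symmetric about 50%. Against a 50% arm the spurious q is 0.439 - 0.407 = 0.032 (70%), 0.439 - 0.361 = 0.078 (80%) and 0.439 - 0.279 = 0.160 (90%). The design values of q are 0.30 and 0.40.

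**3. False rejection by the Fisher-z test.** The expected test statistic is q/sqrt(2/(n-3)); the standard error is 0.144 at n=100 per arm and 0.082 at n=300. The protocol's pilot target is at least 100 per arm; 300 is an assumed larger trial. For 50% against 90% the statistic is 0.160/0.144 = 1.11 and 0.160/0.082 = 1.95, so the chance of exceeding 1.96 in size is about 20% and 50%. Simulation agrees:

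| Shares | n=100 | n=300 |
|---|---|---|
| 50% vs 70% | about 5% | about 6% |
| 50% vs 80% | 8% | 15% |
| 50% vs 90% | 20% | 51% |

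In the same simulations a test of the difference in slopes stays at 4-6%.

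**4. Sensitivity to slope.** A second set of assumptions used independent uniform value scores, which give A an SD of 0.408, and a risk difference of 0.02. Slopes of 2 and 4 are then 2 x 0.408 = 0.82 and 4 x 0.408 = 1.63 logits per SD. For shares of 60% against 90% the spurious q is 0.373 - 0.229 = 0.144 and 0.637 - 0.392 = 0.245. False rejection at n=100 is 16% and 40%; at n=177 it is 27% and 63%. With equal shares it is about 3-6%.

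**5. Sign.** In that second model, slopes of +4 and -4 at a 50% share both give Cox-Snell 0.320, Nagelkerke 0.426 and McFadden 0.278.

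**6. Several pairs (secondary).** Six arms give 6 x 5/2 = 15 pairs. If each were tested at the table's alpha with no true differences, the chance of at least one significant pair is the probability that the range of six standard normal values exceeds sqrt(2) x 1.960 or sqrt(2) x 1.645. These are 36.6% at alpha 0.05 and 56.9% at 0.10. The usual independence formula gives 53.7% and 79.4%, which is too high because pairs share arms.

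**The case against.** **The size is assumed.** This stands. The shares, the slope and the type of R2 are not in the protocol. A 20-point shift near the middle (50% against 70%, or 30% against 50%) does almost nothing, and McFadden R2 moves only from 0.135 to 0.119 between 50% and 90%. However, the only scale the protocol plans on is Fisher Z of R, which is among the more sensitive.

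**RRR is not necessarily penalised.** A reader might infer that RRR, by raising uptake, will be ranked as less congruent. The Background gives a direction and no level. If other arms sit at 20-30% and RRR at 50%, the artefact favours RRR. It works against whichever arm is further from 50%.

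**A reversed slope is unlikely and would be seen.** Largely fair: the Background expects a positive relation, Eq 1 estimates a slope in each arm, and a signed R would keep direction. The rule as written still ranks on R2 with no sign condition.

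**The plan does not state 15 unadjusted tests.** Correct, although a reader might infer them from the G1-against-G2 wording and the table. No count of pairs is given, the table serves the pilot's size, and a multiplicity rule may sit in a statistical analysis plan that is not shown. The familywise figures are therefore conditional.

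**Covariates.** The protocol says "Using a maximum-likelihood model will allow us to adjust for other factors (age, gender, profession) in a natural way". One might infer that R2 inflated by these covariates will be compared between arms; the text does not say so. Nor does it restrict the profession and country tests to main effects.

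**The analysis is provisional.** Also correct: choosing the analysis is a stated aim of the pilot, and Attachment 1 lists alternatives. Those alternatives set no sign condition either.

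**Conclusion.** The concern holds as a weakness of the stated primary comparison. R2 compared between separately fitted arms responds to the share choosing pills as well as to congruence, and it carries no sign. The protocol's own background makes unequal shares likely.

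At 1 logit per SD of A, the effect is negligible for 50% against 70%, modest for 50% against 80% (8% to 15% false rejection at a nominal 5%), and serious for 50% against 90% (20% to 51%). Steeper slopes make it worse, and McFadden R2 would make it small. The direction for any given presentation cannot be predicted from the document. Adjusting for multiple comparisons would not remove this bias.

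The familywise error of about 37% or 57% is secondary and applies only if all 15 pairs are tested at the table's alpha.

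Severity: should be fixed. A stronger rating is not supported, because the Pilot study and Sample size sections leave the final analysis to be settled after the pilot.

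**What to change.** - Make the primary analysis one pooled logistic model, D ~ G + A + G x A, with A as the protocol defines it. Use the likelihood-ratio test of G x A (5 degrees of freedom) as the global test.
- Report each arm's slope with its sign and 95% confidence interval, and require a positive slope before calling an arm congruent.
- Interpret pairs only after the global test, or with Tukey or Holm adjustment.
- Keep R2 as a description and name its type.
- Test consistency between GPs and the public, and across countries, by further interactions with G x A.

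This uses the same data and needs only new analysis wording, but it costs pairwise precision. The Tukey critical value for six arms is about 2.85 instead of 1.96. On the protocol's own scale (q = 0.30, 80% power, alpha 0.05), N per group becomes 2[(2.850 + 0.842)/0.30]^2 + 3 = 305.8, so 306 instead of 177. That figure only shows the order of the cost. The main-trial sample size should be re-derived from the pilot on the slope-difference scale.

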## OBJECTIVES

The primary objective of this study is to determine which of the following ways of presenting information about the reduction in risk of cardiovascular disease (CVD) results in decisions that are most consistent with what individuals considering starting statins for the primary prevention of CVD would be expected to decide based on their expected utilities:

1. RRR - Among those who take the pills there will be a 33% reduced risk of heart disease during the next 10 years.
2. ARR - Among those who take the pills, there will be a 2% absolute reduction in the risk of getting heart disease during the next ten years.
3. NNT – Among 50 people that take the pills for the next ten years there will be one additional person who will not get heart disease during that time.
4. Event rates - Among those who take the pills the risk of getting heart disease during the next ten years will be reduced from 6% to 4%.
5. TNT (tablets needed to be taken)10 – Among 50 people that take the pills for the next ten years, they will swallow a total of 182,500 pills and there will be one additional person who will not get heart disease during that time.
6. Whole numbers11 - Among 100 people who do not take the pills, 94 will not get heart disease and six will get heart disease during the next 10 years. It is not possible to say whether you would be one of the 94 or one of the six. Among 100 people who take the pills, the number who will not get heart disease in the next ten years will increase from 94 to 96 and the number who will get heart disease during the next 10 years, will decrease from 6 to 4.. Again, it is not possible to say whether you would be one of the 96 or one of the four.

Additional questions that this study will address are:

1. What is the effect of these different ways of presenting information about CVD risk reduction on understanding, confidence and satisfaction?
2. Which of the following two ways of eliciting the relative importance of the consequences of starting statins for the primary prevention of CVD gives “expected utilities” that are most congruent with what individuals decide?

- Visual analog scales (VAS’s)
- Likert-type rating scales (LTRS)

1. Are answers to the primary question and the two questions above consistent across patients (the general public) and general practitioners (GP’s)?
2. Are answers to the first three questions consistent across different countries (Norway, USA, Canada and Germany)?

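### The profession coding has no GP-versus-public contrast, and covariate adjustment of Eq 1 does not test whether the answers are consistent across GPs, the public and countries

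*Protocol*

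**What the plan says.** Protocol, Objectives, poses two consistency questions: "Are answers to the primary question and the two questions above consistent across patients (the general public) and general practitioners", and "Are answers to the first three questions consistent across different countries (Norway, USA, Canada and Germany". The answers in question are which presentation is best, the effects on understanding, confidence and satisfaction, and VAS versus LTRS.

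Protocol, Analysis, defines how the primary answer is reached. Eq 1 is a logistic regression of the decision D on the expected-utility difference A; "Eq 1 will be fit for each group G", where G is the presentation. Then: "We will then compare the fit between different groups by comparing the R2 between the different groups".

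Profession and country appear in the paragraph that follows: "Using a maximum-likelihood model will allow us to adjust for other factors (age, gender, profession) in a natural way". This is said to allow tests for professional background, coded "scientists or engineers vs GPs or other health professionals vs others", and for "differences across countries (Canada vs Germany vs Norway vs USA". The reason given is "To the extent that any of these factors are confounders, adjusting for these factors would improve the precision of our model".

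Protocol, Secondary comparisons, says the pilot data cannot serve the comparisons other than VAS versus LTRS, and describes a method for that one only. Attachment 1 offers alternative analyses for the presentations and for VAS versus LTRS, not for profession or country.

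**The concern.** There are two separate mismatches.

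**Coding.** The objective needs GPs on one side and the general public on the other. The three-level factor puts GPs with other health professionals and takes scientists or engineers out of the rest of the public. No pair of its levels is the contrast asked for.

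**Type of test.** Whether an answer is consistent across strata is a question of effect modification: does the A-to-D fit, or the difference in fit between presentations, change with the stratum? A covariate added to Eq 1 shifts the log-odds of taking the pills at a given A. Testing it asks whether one group takes pills more readily. Two groups can differ in that and rank the presentations identically, or agree in it and rank them in opposite order.

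At stake are two stated secondary objectives. If the paragraph is carried forward as it stands, a difference in willingness to take pills could be reported as inconsistency, and a real reversal of the presentation ranking could go unseen. The primary comparison of presentations is not affected.

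**Working it through.** **Step 1. Objective against analysis.**

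| | Objectives | Analysis |
|---|---|---|
| Profession | GPs vs general public | scientists/engineers; GPs with other health professionals; others |
| Country | Norway, USA, Canada, Germany | the same four |
| Quantity compared | the answers, i.e. differences in fit between presentations | adjustment terms in the model for D |

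Profession fails on the first and third rows; country fails on the third only.

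**Step 2. What a covariate term tests.** Write S for the stratum. Adjusting Eq 1 gives logit(D) = b0 + b1·A + c·S. The null c = 0 says that uptake at a given A is equal in the strata. The slope b1 is common to the strata by construction, so the model has no parameter for a different A-to-D relationship. Fitting it separately in each presentation group and comparing c across groups would still compare uptake.

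An illustration, in which every input is an assumption: A standard normal, two presentations by two professions, 200 per cell, 600 simulated trials, likelihood-ratio tests at 0.05.

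| Scenario | Profession covariate rejects | A × presentation × profession rejects |
|---|---|---|
| Better presentation reversed between professions (slopes 0.5/1.5 vs 1.5/0.5), equal uptake | 5.2% | 99.8% |
| Same slopes in both professions, uptake shifted by 0.6 log-odds | 95.5% | 5.7% |

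The rates depend on these inputs. That the two tests answer different questions does not.

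**Step 3. Reproduce the protocol's sample-size table.** Inputs from Protocol, Sample size: q = Z1 − Z2 (Fisher Z), two-sided alpha, equal groups. The variance of Z is 1/(n − 3), so a difference of two has variance 2/(n − 3) and

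N per group = 2·[(z(1−α/2) + z(power))/q]² + 3.

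For alpha 0.05 and power 0.80, (1.960 + 0.842)² = 7.849.
- q = 0.30: 2 × 7.849/0.09 + 3 = 177.4 (stated 177).
- q = 0.40: 2 × 7.849/0.16 + 3 = 101.1 (stated 101).

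All 12 rows reproduce to within one subject. The table is sound for comparing two groups.

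**Step 4. The same method for consistency.** The presentation contrast in GPs minus the same contrast in the public is a difference of two differences, with variance 4/(n − 3), n being the number per presentation-by-stratum cell. Here q is the size of that difference of differences.

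N per cell = 4·[(z(1−α/2) + z(power))/q]² + 3.
- q = 0.30: 4 × 7.849/0.09 + 3 = 351.8, so 352.
- q = 0.40: 4 × 7.849/0.16 + 3 = 199.2, so 200.

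Filling every cell at q = 0.30 would take 6 × 2 × 352 = 4,224 people for profession and 6 × 4 × 352 = 8,448 for country.

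**Step 5. Power with 100 per cell.** 100 is the protocol's pilot minimum per presentation group, borrowed here as a cell size.

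| | standard error | power, q = 0.30 | power, q = 0.40 |
|---|---|---|---|
| Simple comparison | √(2/97) = 0.144 | 55% | 80% |
| Difference of differences | √(4/97) = 0.203 | 31% | 50% |

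**The case against.** The strongest reply is that the plan is openly provisional. Protocol, Pilot study, says the pilot will help decide how to analyse the data, and Sample size repeats that this is unsettled. The pilot recruits only the US public, so GP and country comparisons come later. The protocol never uses the term main effects, writes no equation with covariates and does not rule out interactions; a statistical analysis plan could supply them.

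Much of this stands. A reader might infer that the protocol commits to a main-effects test and excludes anything else. It does not say so; that is the natural reading of adjusting and then testing for differences, with confounding and precision as the reason. But the point is not mere silence. The protocol fixes a profession factor that disagrees with its own objective, and no section forms the GP-versus-public contrast or a comparison within strata.

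A reader might also infer that the pooled category makes the GP question unanswerable. The documents do not support that: GPs are invited by their own route and participants answer questions about themselves, so separate coding looks feasible.

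Nor can the harm of pooling be given one number. Suppose, purely as an assumption, 150 per group and slopes of 1.3 for GPs and 0.4 for the public. A two-way A × group test then has about 89% power with GPs alone. With GPs at 50% or 30% of the pooled level, it falls to about 30% or 12–14% if other health professionals behave exactly like the public, and does not fall if they behave like GPs. The protocol gives no basis for choosing, and this two-way test is not the comparison between presentations that the objective needs.

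Finally, the remedy is demanding. Testing a difference of differences is much less precise, and a test on slopes alone would leave the plan's R2 measure. Both objections are right and shape the fix.

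**Conclusion.** The point holds for two secondary objectives and should be corrected. The coding conflict for profession is explicit in the text. The mismatch between adjustment and consistency rests on the natural reading of the Analysis paragraph; it applies to profession and country alike, and for country it is the only defect. The primary analysis and the sample-size table need no change on this account.

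On size: a consistency test needs about twice the number per cell that the simple comparison needs per group (352 against 177 at q = 0.30; 200 against 101 at q = 0.40), and has about 31% power at q = 0.30 with 100 per cell. These figures assume equal cells, independent strata and the protocol's Fisher Z approximation for R. The simulated rejection rates are illustrative only; they depend on the assumed slopes and, where categories are pooled, on how closely other health professionals resemble GPs.

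**What to change.** In Protocol, Analysis:

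1. Make GPs a category of their own, keep other health professionals separate, and define the general public. Name GPs versus the general public as the contrast.
2. Judge consistency on the plan's own measure. Within each stratum, compare Fisher Z of R between presentations; then test the difference of those differences between GPs and the public, and across the four countries, with estimates and intervals. An A × presentation × stratum interaction can be supportive.
3. Do the same for VAS versus LTRS. All participants complete both, so the two R's within a stratum are correlated and the standard error must allow for this. For understanding, confidence and satisfaction, use presentation × stratum terms.
4. Keep profession and country covariates for adjustment only.
5. State that the consistency comparisons have limited precision, quoting the figures above, and that a non-significant result will not be read as proof of consistency.

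The cost is mainly wording, plus a check that the questionnaire records being a GP separately from other health professions. The real price is statistical. Unless the final sample size, which the protocol still leaves open, is set for these contrasts, they will be reported as imprecise estimates.
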